##### Data analysis

All baseline patient characteristics will be analyzed descriptively. Continuous variables will be described as means with standard deviation or as medians with interquartile range, minimum, and maximum. Categorical variables will be described in absolute and relative frequencies.

The sum of the health system and information dimension score of SCNS-SF34-G is defined as the primary outcome of the RCT. The primary outcome at t1 will be analyzed using a linear model in which the outcome value is included as dependent variable and the respective baseline value and the treatment group as independent variables. Missing values in the primary outcome will be replaced by multiple imputation, which consider treatment the group and primary outcomes at t0 as independent variables using the fully conditional specification method [57]. A complete case analysis will be performed as an additional sensitivity analysis. The respective parameter estimates will be reported together with *p* values and 95% confidence intervals. The analysis of the primary outcomes at t2 and t3 will be done analogously to the primary linear model. The analyses of the secondary outcomes will be performed using linear (for continuous outcomes) or generalized linear models (for binary outcomes). The models include the outcome value at follow-up time t1, t2, or t3 as the dependent variable. The respective parameter estimates will be reported alongside descriptive *p* values and 95% confidence intervals. *p* values smaller than 0.05 will be considered statistically significant. Analysis will be done using the statistical software SAS v9.4 (SAS Institute, Cary, NC).

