##### Data collection

Recruitment of patients and caregivers will take place at the Department of Thoracic Oncology, University Hospital Heidelberg. Patients and caregivers will be approached by a study nurse who works at the department. If patients and caregivers are interested in the project, they will receive oral and written information about the study. After giving consent, baseline (t0) questionnaire data will be collected before patients are randomly assigned to a group. The first milestone conversation (tandem or standard communication with a physician) will then take place. For the follow-up, questionnaires will be distributed after 3 (t1), 6 (t2), and 12 (t3) months (Fig. 1). Study plan according to SPIRIT-checklist see Fig. 2 and Additional file 2. Patient documents will be checked by a study nurse for adverse events. No adverse events are anticipated.

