##### Power calculation

With a sample size of *n* = 100, a difference of 5 points on a scale from 0 to 100 for the primary outcome can be shown using a two-sided *t*-test at a significance level of α = 0.05 with a power of 1 – ß = 0.85, assuming a standard deviation of σ = 7.4 [58]. A dropout rate of 18.5% is taken into account. Prognoses of metastatic lung cancer and the experiences at the Department of Thoracic Oncology, University Hospital Heidelberg have shown that 82.5% of the patients are still alive after 3 months and 75% are still alive after 6 months. It can be assumed that the additional variance explained by the inclusion of the baseline value as a covariate will lead to increased power. The sample size calculation was performed using SAS v9.4 (SAS Institute, Cary, NC).

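### The imputation model uses only the analysis model's own covariates, so multiple imputation reproduces the complete-case result and their agreement is no evidence of robustness to drop-out

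*Protocol article*

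**What the plan says.** All of this is in the Protocol article, in the part on the pragmatic RCT.

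- **Analysis model (Data analysis).** The score at 3 months (t1) is analysed by "a linear model in which the outcome value is included as dependent variable and the respective baseline value and the treatment group as independent variables". The 6- and 12-month scores (t2, t3) are to be analysed in the same way.
- **Imputation (Data analysis).** "Missing values in the primary outcome will be replaced by multiple imputation", with a model "which consider treatment the group and primary outcomes at t0 as independent variables using the fully conditional specification method". I read the garbled phrase as the treatment group and the t0 score.
- **Sensitivity analysis (Data analysis).** "A complete case analysis will be performed as an additional sensitivity analysis". The article names no other.
- **Timing of baseline (Data collection).** "baseline (t0) questionnaire data will be collected before patients are randomly assigned to a group".
- **Expected losses (Power calculation).** "A dropout rate of 18.5% is taken into account", and "82.5% of the patients are still alive after 3 months and 75% are still alive after 6 months".

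The trial also collects FACT-L, PHQ-4, the Distress Thermometer and the other supportive-care-needs domains (Instruments). None is named as a predictor in the imputation model.

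**The concern.** Multiple imputation improves on complete cases when it brings in information that the analysis model lacks. Here the imputer and the analyst use the same two variables, so nothing is brought in. The named sensitivity analysis makes the same missing-data assumption as the primary analysis and will agree with it whatever the drop-out process.

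At stake is how that agreement is read. In metastatic lung cancer, patients who are more symptomatic or distressed may be less likely to return a form. The arms may also differ in this: monthly nurse follow-up belongs to the intervention (Table 1), and those nurses work only in the intervention arm (Limitations and strengths). The document does not say that return rates will differ. If they did, for reasons not captured by arm and baseline score, both analyses would be off by the same amount and neither would show it.

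**Working it through.** **1. The plan's own figure.** Inputs from Power calculation: difference 5, SD 7.4, two-sided α 0.05, power 0.85, drop-out 18.5%.

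- Normal approximation: n per arm = 2 × (1.960 + 1.036)² × 7.4² / 5² = 39.3, so 40. Total 80 / (1 − 0.185) = 98.2, so 99.
- Exact t-test: 41 per arm. Total 82 / 0.815 = 100.6, so 101.
- With 41 + 40 evaluable patients the exact power is 0.852.

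The planned 100 is reproduced and is not in dispute.

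**2. Why the two analyses coincide.** Let X hold intercept, group and t0 score, with rows split into observed (o) and missing (m) outcomes. Complete-case ANCOVA gives b = (X_o′X_o)⁻¹X_o′y_o. Proper imputation draws the missing outcomes around X_m b on average. The completed-data estimate then averages to

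(X′X)⁻¹(X_o′y_o + X_m′X_m b) = (X′X)⁻¹(X_o′X_o + X_m′X_m) b = b.

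This needs no assumption about why outcomes are missing. It needs only a complete t0 score and an imputation model with the same predictors as the analysis model.

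**3. Simulation check.** 600 trials per scenario, N = 100, true effect −5, SD 7.4, 18–19% missing at t1, 50 imputations. Assumed, not in the document: baseline–outcome correlation 0.5; an auxiliary measure, seen for everyone, correlated 0.6 with the residual; logistic drop-out. The last column adds the auxiliary to the imputation model (20 imputations).

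| Drop-out depends on | Complete case | MI as planned | MI + auxiliary |
|---|---|---|---|
| nothing | −5.09 | −5.09 | −5.09 |
| baseline score | −4.98 | −4.99 | −4.99 |
| auxiliary, one arm only | −4.03 | −4.03 | −4.92 |
| outcome itself, one arm only | −3.79 | −3.79 | −4.19 |

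- Complete case and planned MI correlate at 0.998, with a mean absolute difference of about 0.07 points.
- MI standard errors are no smaller (1.443 against 1.435 in the first scenario).
- In one data set with 20,000 imputations, MI gave −6.107 and complete case −6.108.
- The shared bias in the last two rows is 5 − 4.03 = 0.97 and 5 − 3.79 = 1.21 points.

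A separate simulation (1,500 trials per scenario, 21–25% missing, same 0.6 residual correlation) gave a correlation of 0.997. With auxiliary-dependent drop-out in one arm, the biases were 0.111 SD (complete case) and 0.112 SD (planned MI): 0.111 × 7.4 = 0.8 points, or 0.8 / 5 = 16% of the target.

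**4. How much of the t1 loss is non-response?** Deaths by 3 months: 100 − 82.5 = 17.5%. Allowed drop-out: 18.5%. Living non-responders on these figures: 18.5 − 17.5 = 1 patient in 100. Take an extreme case: that patient is the most extreme of about 41 in one arm (about 2.2 SD on the auxiliary), with the same 0.6 and 0.5 correlations. The arm mean shifts by about (2.2 / 40) × 0.6 × 0.87 = 0.03 SD, or 0.03 × 7.4 = 0.2 points.

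**5. Later visits.** Deaths by 6 months: 100 − 75 = 25%. No 12-month figure is given, but the Background puts median survival below 12 months, so more than half may have died by t3. Missing data grow and the same method is carried forward.

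**The case against.** Several counter-arguments have force.

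- **A reader might infer that neither analysis can cope with any informative drop-out.** The check does not support that. Both handle drop-out that depends on arm and baseline score (−4.98 and −4.99 against −5). The planned ANCOVA is valid under that missing-at-random assumption.
- **A reader might infer that the primary result will be biased by 0.8 points, or 16% of the target.** The document supports no such figure. It rests on informative drop-out in one arm only, an assumed 0.6 correlation and 21–25% recoverable non-response. Other assumptions gave 1.0 to 1.2 points. On the protocol's planning figures about one patient in 100 is a living non-responder at t1, and the extreme case is then about 0.2 points. Nor does the document say that FACT-L, PHQ-4 or the Distress Thermometer predicts drop-out or information need.
- **A reader might infer that no other sensitivity analysis exists.** The article calls complete case an additional one and does not say it is the only one; a fuller analysis plan may hold more. But the article does fix the imputation predictors and does name complete case as the check, and those two choices can be judged as stated.
- **Fully conditional specification might suggest a richer chained model.** If other incomplete variables or later scores entered, the equivalence would break. The text names only group and t0 score. Missing t0 values could also open a small gap, but t0 is collected before randomization.
- **Auxiliary variables are no cure.** With outcome-dependent drop-out they moved the estimate only from −3.79 to −4.19. A large model fitted by arm, on about 41 observed patients each, would be strained.

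The equivalence itself survives all of these.

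**Conclusion.** The point holds in limited form. As written, and with t0 essentially complete, the multiple imputation reproduces complete-case ANCOVA apart from Monte Carlo noise. Agreement between the two is built in and should not be reported as robustness to drop-out related to symptoms, distress or the unseen outcome. That conclusion depends on no assumed mechanism.

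The size of any bias does. It was roughly 0.8 to 1.2 points of the 5-point target in illustrative simulations with about 18–25% non-response, and far less at t1 if nearly all loss is death. The matter weighs more at t2 and t3, where more data will be missing, although the document does not say how much of that will be non-response by living patients. For deaths, the current text draws no distinction and would impute a score under the same assumption.

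This is worth correcting before analysis, but it does not invalidate the primary model. The article itself calls the trial an initial exploration.

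**What to change.** - For living non-responders, add a short prespecified list of t0 measures already collected to the imputation model, for example FACT-L, PHQ-4 and the Distress Thermometer. Do not fit a large model separately by arm.
- Make a delta-adjusted (tipping-point) analysis the sensitivity analysis, so that the check departs from missing at random. Keep complete case as descriptive.
- State how missingness due to death is handled, separately from questionnaire non-response, at t1, t2 and t3.

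**Cost.** No new data: a few lines of SAS and some wording, a slightly larger imputation model at n = 100, and a little more analysis work.

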##### Power calculation

With a sample size of *n* = 100, a difference of 5 points on a scale from 0 to 100 for the primary outcome can be shown using a two-sided *t*-test at a significance level of α = 0.05 with a power of 1 – ß = 0.85, assuming a standard deviation of σ = 7.4 [58]. A dropout rate of 18.5% is taken into account. Prognoses of metastatic lung cancer and the experiences at the Department of Thoracic Oncology, University Hospital Heidelberg have shown that 82.5% of the patients are still alive after 3 months and 75% are still alive after 6 months. It can be assumed that the additional variance explained by the inclusion of the baseline value as a covariate will lead to increased power. The sample size calculation was performed using SAS v9.4 (SAS Institute, Cary, NC).

#### Effects on patients and caregivers (semi-structured interviews)

Experiences with the MCA concept regarding empathy and shared decision-making will be evaluated through interviews with patients and caregivers.

##### Sample and sample size

Patients and caregivers who will experience MCA will be approached in the hospital setting. Patients and caregivers must be over 18 years old and able to understand and speak German well. They will be asked to participate and receive a written invitation to the study, including the background information, participation details, and informed consent form. About 12 patients and 12 caregivers will be interviewed, possibly more, until data saturation is reached.

##### Data collection

Semi-structured interviews will be conducted at the Department of Thoracic Oncology, University Hospital Heidelberg, after at least two milestone conversations have taken place. A theory-based topic guide with open-ended questions will be used. Interviews will be digitally recorded and transcribed verbatim [59].

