### Phase 3: outcome evaluation

#### Impact of MCA on patient outcomes

The effects of MCA on patients and caregivers will be determined in a RCT. Their experiences with the concept will be assessed in semi-structured interviews. The effects on interprofessional collaboration will be evaluated in a longitudinal observational study with healthcare professionals.

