##### Sample and sample size

The study will consist of 100 patients and 100 caregivers named by the patients. It will include patients with newly diagnosed metastatic lung cancer (stage IV) who are at least 18 years old, able to give consent, have a good knowledge of the German language, and are willing to participate. Participating caregivers also must be at least 18 years old, have a good understanding of the German language, be willing to participate, and give consent.

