##### Randomization procedure

The randomization into the groups (intervention and control) will occur in the ratio 1:1. Block randomization will be performed to ensure equal-sized groups. The randomization will be performed using sealed opaque randomization envelopes, which will be provided by the Institute of Medical Biometry and Informatics Heidelberg.

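### The interview rule lets MCA-arm trial patients be interviewed before the 3-month primary assessment, while controls have no equivalent contact

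*Protocol article*

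**What the plan says.** All references are to the protocol article.

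- **Timing of interviews.** In the semi-structured interviews part, Data collection places them "after at least two milestone conversations have taken place". No calendar window is given and t1 is not mentioned.
- **Who is interviewed.** Sample and sample size in the same part says "Patients and caregivers who will experience MCA will be approached in the hospital setting". On numbers it says "About 12 patients and 12 caregivers will be interviewed, possibly more, until data saturation is reached".
- **Link to the trial.** Under Impact of MCA on patient outcomes, directly after the sentence on the RCT, the article says "Their experiences with the concept will be assessed in semi-structured interviews".
- **The trial.** "The study will consist of 100 patients and 100 caregivers named by the patients", and "The randomization into the groups (intervention and control) will occur in the ratio 1:1". After baseline and the first milestone conversation, "questionnaires will be distributed after 3 (t1), 6 (t2), and 12 (t3) months".
- **Primary analysis.** "The primary outcome at t1 will be analyzed using a linear model", with the baseline value and treatment group as covariates.
- **Content.** The part's introduction names empathy and shared decision-making as interview topics. The Abstract adds communication needs and further use of services.
- **Milestones.** There are four, tied to the course of disease (diagnosis, stable phase, progression, transition to best supportive care). The first follows randomization directly.

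**The concern.** The condition that opens the interview is a care event, not a trial time point. A patient whose disease moves quickly could complete two milestone conversations, and so qualify, before month 3. The interview is a research contact. It is not among the MCA components in Table 1, and only people who experience MCA receive it.

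Its topics lie close to the primary outcome, patients' information needs, and to perceived empathy and service use among the secondary outcomes. Talking through one's communication needs could raise new questions or leave a patient feeling better heard. Either could change a score that the patient reports unblinded. If that happened in one arm before t1, the change would be counted as an effect of MCA.

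The Limitations and strengths section already concedes possible bias for this endpoint because patients know that they are in a trial and know its purpose. A contact given to one arm only is a separate source, and an avoidable one.

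**Working it through.** **1. The plan's own sample size.** Inputs from Power calculation: difference 5 on a 0–100 scale, SD 7.4, two-sided α = 0.05, power 0.85, dropout 18.5%. An exact two-sample t-test needs 41 per arm (power 0.856), or 82 in total. Allowing for dropout, 82 / 0.815 = 100.6. With the stated 3-month survival instead, 82 / 0.825 = 99.4. The planned 100 reproduces, and this point does not affect it.

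**2. Are interviewees trial participants?**

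- *For:* the sentence on experiences follows directly on the RCT. The Abstract gives 100 patients for the whole project and the RCT alone has 100. About 12 interviewees from outside the trial would make about 112.
- *Against:* the interviews have their own invitation, consent form and eligibility (over 18, good German), with no stage IV or new-diagnosis criterion. Milestone conversations are documented from the kickoff of implementation, so MCA patients outside the RCT may exist. The Abstract's count also omits the 100 caregivers, so it is not a complete tally.

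Trial membership is the better reading, but it is an inference.

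**3. Can the second milestone precede t1?** No dates are given. The article expects 17.5% of patients to have died by 3 months (1 − 0.825) and 25% by 6 months, so early progression or transition conversations are foreseeable. How many there would be cannot be derived.

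**4. Exposed share of the MCA arm.** 1:1 allocation of 100 gives 50 per arm.

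- Ceiling, with all 12 in the trial and all interviewed before t1: 12 / 50 = 24%. If all 12 are among those expected alive at t1 (0.825 × 50 = 41.25), 12 / 41.25 = 29% of that group.
- Half of them: 6 / 50 = 12%.
- None: 0%.
- The number of interviews is open upwards, so 24% is the ceiling only for the planned 12.

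**5. Effect on the comparison.** Let *f* be the exposed share and *s* the mean shift per interviewed patient. The arm difference moves by *f* × *s*. The documents give no value for *s*, so 1, 2, 3 and 5 points are assumed. With 41 analyzed per arm and the SD unchanged, the standard error is 7.4 × √(2/41) = 1.63. At *f* = 0.24:

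| Assumed *s* (points) | Move in arm difference | Power for a true 5-point effect, shift against MCA | Same, shift favouring MCA | Two-sided rejection rate with no true effect |
|---|---|---|---|---|
| 0 | 0 | 0.856 | 0.856 | 0.050 |
| 1 | 0.24 | 0.821 | 0.886 | 0.052 |
| 2 | 0.48 | 0.780 | 0.912 | 0.060 |
| 3 | 0.72 | 0.735 | 0.933 | 0.072 |
| 5 | 1.20 | 0.632 | 0.963 | 0.112 |

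At *f* = 0.12 the move is 0.12 to 0.60 points and the rejection rate 0.051 to 0.065. At 12/41 it is 0.29 to 1.46 points and 0.054 to 0.143.

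**The case against.** The strongest reply is that this is scheduling detail which a condensed article may leave to the full protocol, and that two conversations are only a minimum experience requirement, not an instruction to interview at once. It is true that nothing here contradicts another section. But the article does state a timing rule, and that rule as written permits an interview before t1.

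A second reply is that trial membership is not stated and milestone dates are absent. This stands in full. A reader might infer that about a quarter of the MCA arm will be interviewed before the primary outcome. The documents do not support that. It needs every interviewee to be a trial patient, every second milestone to fall within 3 months, and every interview to precede t1.

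Third, a 5-point shift would make a single interview as strong as the whole target effect, and individual shifts may partly cancel. This also stands. At 1 to 2 points, even the 24% ceiling takes the rejection rate under no effect only to 0.052–0.060. The MCA arm also already has monthly nurse contacts, and the interview topics overlap the information-needs scale only in part. A reader might conclude that the primary result will be biased in MCA's favour, but neither the size nor the direction of any effect can be taken from the documents.

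Finally, waiting for t1 loses the views of patients who die early. That is a real cost to the qualitative work.

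**Conclusion.** The point holds as a cheap improvement to the design, not as a demonstrated bias. What rests on the text alone is that the rule permits an interview before t1, that interviews are confined to people who experience MCA, and that no control contact is described. That the interviewees are trial participants is the better reading but remains an inference. The exposed share is bounded only loosely, between none and about 24% of the MCA arm for 12 interviews. Any consequence depends on an assumed shift: negligible at 1 point per interviewed patient, and material only if the shift is several points and most interviews fall before t1.

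**What to change.** Add to Data collection in the semi-structured interviews part:

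> For participants in the randomized trial and their caregivers, the interview is held only once two or more milestone conversations have been completed and the t1 questionnaire has been returned or its window has closed. The date of each interview is recorded.

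This costs one sentence and one recorded date. It removes the one-arm contact before the primary assessment and changes nothing if the interviewees turn out to come from outside the trial. About 41 MCA patients are expected alive at 3 months, so around 12 interviews should remain reachable. The price is that patients who die before month 3 (about 17.5%) cannot be interviewed, and early transitions to best supportive care may be concentrated among them. The interview report should state this limitation.

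Do not pair this with a t2 or t3 analysis that leaves out interviewed patients. They exist only in the MCA arm and are selected after randomization, by reaching two conversations and agreeing to be interviewed. Removing them from one arm would break the randomized comparison.
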